## Abstract

**Introduction:**

The situation for women experiencing mental health problems during pregnancy and postpartum in rural India is critical: a high burden of disease, a high estimated number of women are undiagnosed and untreated with mental health problems, a substantial gap in research on women's perinatal health, and severe stigma and discrimination. The SMARThealth Pregnancy study is a cluster randomised trial using a digital intervention to identify and manage anaemia, hypertension, and diabetes in the first year after birth in rural India. Within this study, the SMARThealth Pregnancy and Mental Health (PRAMH) study is a situational analysis to understand mental health problems during pregnancy and in the first year following birth in this population.

**Methods/design:**

This situational analysis aims to analyse and to assess the context of perinatal mental health, health services, barriers, facilitators, and gaps in Siddipet district of Telangana state in India, to develop an implementation framework for a future intervention. A tested, standardised situational analysis tool will be adapted and applied to perinatal mental health in rural India. A desktop and policy review will be conducted to identify and analyse relevant mental health and pregnancy care policies at the national and state levels. We will conduct in-depth interviews with policymakers, planners, mental health professionals and other experts in perinatal mental health (*n* = 10–15). We will also conduct focus group discussions with key stakeholders, including women with perinatal mental health problems, their families and carers, and community health workers (*n* = 24–40). A theory of change workshop with key stakeholders will be conducted which will also serve as a priority setting exercise, and will clarify challenges and opportunities, priorities, and objectives for a pilot intervention study. The analysis of qualitive data will be done using thematic analysis. Based on the data analysis and synthesis of the findings, an implementation framework will be developed to guide development, testing and scale up of a contextually relevant intervention for perinatal mental health.

**Discussion:**

The situational analysis will help to establish relationships with all relevant stakeholders, clarify the context and hypotheses for the pilot intervention and implementation.

## Introduction

Pregnancy and the first year after childbirth are a sensitive period for mothers, with frequent experiences of emotional distress. Globally, up to 20% of women experience mental health problems during pregnancy, and prevalence is significantly higher for women in low- and middle-income countries (LMICs) than those in high-income countries (HICs) (1). In LMICs, the prevalence of specific mental disorders ranges from 19% for perinatal depression (2), to 34% for antenatal anxiety and 26% for postnatal anxiety (3). A recent systematic review among women in India found that the overall pooled estimate of the prevalence of antenatal common mental disorders (CMDs) was around 22% (4).

Particularly vulnerable are women with a history of previous mental health conditions, and those exposed to synergistic health problems within the context of persistent social and economic inequalities (as described in the concept of syndemics) (5), such as poverty or intimate partner violence and crises of health and safety (6–8). Across India, lower socioeconomic status, poor education, unemployment, and bad relations with in-laws are correlated with mental health conditions in perinatal women (9, 10). In rural India, a study in perinatal mothers found that predictors of maternal psychological distress were infant loss, an unwanted pregnancy, health problems and socioeconomic disadvantage (11). Additional risk factors for maternal depression found across India, are having a previous girl child, the desire or pressure to have a male child, and the birth of a female baby (12, 13).

Suicide has been noted to be a leading cause of death in the perinatal period (14), in LMICs particularly young women aged 15–19 years are at risk (15). Even though pregnancy is generally thought to have a protective effect during this period against suicide for mothers, it was found that this was reduced during and after pregnancy for women below the age of 20 years, or those where a pregnancy ends in stillbirth, miscarriage, abortion, or was unwanted (16). In India, specific socio-cultural factors influence the risk for suicide in perinatal women. For instance, increased risks may arise due to infertility, or in relation to unlawful, but still widely practiced, gender birth control methods in order to obtain an often-preferred male child (16, 17). Suicidality amongst antepartum mothers in early pregnancy (<20 weeks) was found to be 7.6% in a sample from South India (18). The study also found that depression severity and a history of suicidal ideation were the strongest predictors of suicide and calls for urgent mental health assessment in women during pregnancy.

Perinatal mental health conditions are correlated with physical disorders, such as gestational hypertension and preeclampsia (19, 20), gestational diabetes (21, 22), preterm birth (23, 24), miscarriage (25), and chronic physical health conditions (26). Conversely, perinatal mental health problems can also lead to difficulties in maternal selfcare, social relationships, and in challenges in infant bonding, breastfeeding and bringing up the child (27, 28).

Perinatal mental health problems can severely affect the infant before and after birth. Perinatal mental health problems correlate with low infant birth weight, restricted foetal growth, as well as social, emotional, behavioural and cognitive development of the child and changes in brain structures and functioning of the child (29, 30). For instance, higher perinatal depressive symptoms have been found to lead to premature brain development in children, including reduced thickness and diffusivity of their brains (31).

Stigma and discrimination are key contributors of distress and harm experienced by people living with mental health conditions, which are inhibiting help-seeking, access to care, and the effectiveness and continuity of treatment. In India, women living with mental health problems during pregnancy are frequently experiencing stigma and discrimination (32), and, in addition, they are often facing intersectional stigma due to their lower status in society (33).

In recent years, mental health and perinatal mental health have gained more attention globally. However, research evidence on the prevalence of perinatal mental health and effective interventions in LMICs generally, and India specifically, remains scarce (34–36). In India, two meta-analyses estimated that pooled prevalence of antenatal depression was 17.7% (37) and 22% and for postpartum depression (38). Evidence on perinatal anxiety in LMICs is rare, only one recent meta-analysis found that the pooled prevalence of self-reported antenatal anxiety was 29.2% and 24.4% for postnatal anxiety, while the prevalence of clinically-diagnosed anxiety disorder was 8.1% antenatally and 16.0% postnatally (39). The evidence gap on perinatal mental health in most LMIC remains substantial, particularly in the lowest income countries, and calls have been made for more research, to better support women in this critical period of their and their children's lives (1, 39). More recently, a few studies started to explore women's antenatal and postnatal mental health in India and developing culturally appropriate measurement tools (1, 40), however they stress that there remains a substantial gap in screening of perinatal women for mental health, and of culturally appropriate, locally validated interventions to address PMDs. Other studies have trialled digital interventions across several states in India which aim to also alleviate the workload from community health care workers (41, 42), however they were not targeting women's mental health, and reach is limited as mobile phones are only available to around 18% of women in rural areas. Recently, the World Health Organisation (WHO) has published a comprehensive guide for integrating mental health into maternal and child health services (43), and guidelines for providing mental health care in community settings are available (27, 44). Peer-delivered, low-intensity psychological intervention could be a cost-effective and potentially effective intervention to support women in their perinatal mental health (45), however there is no evidence for perinatal mental health group interventions in India. In summary, it is not known which interventions are effective, feasible and acceptable to support women who are experiencing mental health conditions during pregnancy and in the year after birth in their communities in rural India.

The SMARThealth Pregnancy (SHP) study is a large 4-year cluster randomised trial (funded by UKRI, see also https://www.wrh.ox.ac.uk/research/smarthealth-pregnancy-improving-women2019s-life-long-health-in-rural-india), across two districts in Telangana and Haryana aiming to reduce anaemia, diabetes, and hypertension in the last trimester and in the first year after birth and identify women at highest risk of longer-term cardiovascular complications. SMARThealth Pregnancy, has been developed to improve the screening, diagnosis, management and postnatal follow-up of women with high-risk pregnancy conditions living in rural India (46). The technology uses the George Institute's SMARThealth platform, extensively tested in India, Indonesia, Thailand, China, and Australia (47–49). The SMARThealth technology has also been applied to mental health in populations in India (50). The platform trains and equips community health workers with screening tools for high-risk conditions, with a decision support algorithm and referral guide based on local guidelines and best practices. The platform facilitates follow-up visits based on the priority of the patient. A primary care doctor App within the platform is paired with the community health worker app, facilitating bi-directional communication. The doctor app also contains prescribing guidelines based on local guidelines and best evidence. The system creates a secure electronic health record and allows for data analytics at the provider, local and district level. SMARThealth Pregnancy presents a unique opportunity for incorporating a perinatal mental health intervention. Before introduction however, it is important for such an intervention to be co-designed and relevant to the wider policy, health system and cultural context before it can be tested and introduced into a specific setting.

We therefore aim to understand the situation and context of perinatal mental illness in rural India. This will be a first critical step in assessing and developing targeted interventions to support women experiencing mental health conditions during their perinatal period. In this study, context refers to concepts used in global mental health (51), including but not limited to, formal and informal perinatal mental health and care systems and services, policies and legislation, social and political context, and cultural values and norms, as well as stigma and discrimination. In addition, we aim to understand what relevant cultural values and norms in relation to perinatal mental health exist in communities in rural India, and to assess the factors, barriers, and facilitators, including stigma and discrimination.

This study will help to understand the situation and context of perinatal mental health for women living in rural India. To start with, we will focus on the state of Telangana where the SMARThealth Pregnancy intervention is currently being tested, with the aim of identifying current barriers, facilitators, and gaps so as to inform development of a future perinatal mental health intervention, which can then be adapted and scaled up more widely across India.

### Aims

The primary aim of the SMARThealth PRegnancy And Mental Health (PRAMH) study is to understand the context of, and assess facilitators, barriers, and gaps for perinatal mental health, in India, specifically in Telangana. The secondary aims are to establish relationships and collaborations with key stakeholders in the field, specifically including people with lived experience, and to develop a synthesis and generate hypotheses for the design and implementation of a new perinatal mental health intervention to be incorporated into the SMARThealth Pregnancy program.

## Methods

### Study design

We will conduct a cross-sectional situational analysis on perinatal mental health using both primary and secondary data. Situational analysis is a suggested methodology for analysing complex systems, such as health systems, and their contexts (52). The method has been previously successfully applied to perinatal mental health (53). This study will be primarily using qualitative methods.

As a first part of the situational analysis, a desktop and literature review will be conducted to assess the sociodemographic and economic context, maternal health and mental health policies and legislation, and perinatal mental health policies and plans. Secondly, interviews and focus group discussions will be carried out to understand gaps identified from the literature review and understand barriers and challenges in implementation. Thirdly, a theory of change workshop with key stakeholders will be conducted to synthesise the findings.

### Study setting

This qualitative study will be conducted in India, specifically in the state of Telangana, in South India. Telangana is a relatively new state in South India (after separating from Andhra Pradesh in 2014) with a total population of 35 million (as per 2011 census), 60% of whom are living in rural areas (54). The maternal mortality rate in Telangana has been reported in the periodic sample registration system (SRS) 2016–2018 as 63 per 100.000 live births, which is comparably low to the national average of 113 (55).

The study setting has been chosen as this is a site in which the SMARThealth Pregnancy trial is currently being run, and thus we have established relationships with ASHA workers, primary care centre staff, and district medical officials. The site is suitable as it has a high prevalence of mental health conditions compared to the national average, for instance for depression, the ratio of Telangana's state Disability Adjusted Life Years (DALY) to median DALY rate for all states is 756 (527–1025), compared to 550 (390–748) for India (56). For anxiety, the rate for Telangana DALY is 324 (228–434), compared to 309 (220–414) for India. Telangana has a developing health system (57), and cultural and gender context and challenges, which can be seen as representative for India (58).

Traditionally a 6-week post-partum period is considered as the postnatal phase, but in order to capture late maternal deaths and to prevent ill health and promote long-term physical and mental health, it is more appropriate to understand the period until up to 1 year after birth as the postnatal period (59).

### Sampling

Participants of the study will be selected through purposeful sampling, using key experts already involved in the SMARThealth Pregnancy programme and pursuing a snowballing approach. In addition, further key experts in the field will be identified and included as participants throughout the completion of the situational analysis tool.

### Participants

Key stakeholders related to rural and semi-rural primary health care (PHC) centres from Siddipet district (Telangana) will be selected to participate in the study, based on either their background in perinatal mental health, interest to engage with the PRAMH study, or role in providing primary health care. Purposive selection of two PHCs will be done, to represent both urban and rural communities. Key stakeholders will include women with lived experience of perinatal mental health problems, community health workers, known as Accredited Social Health Activists (ASHAs), Auxiliary Nurse Midwives (ANMs) and Anganwadi Workers (AWWs), as well as district medical officers, psychiatrists, and psychologists.

### Recruitment and consent

Participants will be identified through the situational analysis, existing personal contacts, and snowballing. Specifically, contacts and stakeholders from the SHP study will be contacted and invited if they qualify for the PRAMH study. Eligible participants will be women with lived experience of perinatal mental health problems, who will be identified by ASHAs and ANMs. Women with lived experience will also be approached through the SHP2 study, if they score highly on the baseline PHQ-9 or GAD-7 or report a mental health history in the screening. We will also invite the women's families/carers, perinatal and mental health care professionals and community health workers, including ASHAs, ANMs, and Anganwadi Workers (AWWs). In addition, policymakers, planners, state and district level health officials, mid-level providers of the new health and wellness centers (HWCs), panchayat village heads, mental health specialists, primary care providers, maternal healthcare providers, AYUSH (Ayurveda, Yoga & Naturopathy, Unani, Siddha and Homoeopathy) doctors, nurses, and civil society organisations, will be invited to participate.

Participants for the interviews and focus groups will be recruited through contacts and the existing network of the SHP study (ASHAs, ANMs, health care providers, researchers, etc., in Telangana). We will work with the participating PHCs and district health authorities before commencement of the study to strengthen relationships. See Table 1 for details.

**Table 1 T1:** Overview of recruitment of key stakeholders in Telangana.

Key stakeholder	Method of data collection	*n*	How they will be approached
Policymakers and planners			
Policymaker	In-depth interview	1–2	The study teams and their contacts will reach out to people that are known to them through the SMARThealth Pregnancy study and through the wider network of the George Institute in India; additional relevant participants will also be identified through the scoping review.
District health official/planner	In-depth interview	1–2	
Panchayat village head	In-depth interview	1–2	
Mid-level provider	In-depth interview	1–2	
Health professionals			
Psychiatrist	In-depth interview	1–2	
Psychologist	In-depth interview	1–2	
Obstetrician/gynaecologist	In-depth interview	1–2	
PHC doctor	In-depth interview	1–2	
AYUSH doctor	In-depth interview	1–2	
ASHAs	Focus group discussion	10–15	
Anganwadi workers, ANMs, nurses	Focus group discussion	10–15	
People with lived experience and community			
Women with lived experience	Focus group discussion	10–15	The women will be identified and approached by the ASHAs and ANMs affiliated with each PHC, and through the SHP2 study, if they score high on the baseline PHQ-9 or GAD-7 or report a mental health history in the screening.
Family members, care givers, community members	Focus group discussion	10–15	The women's families, caregivers, and community members will be identified by the ASHAs and ANMs affiliated with each PHC.
Civil society organisation	In-depth interview	1–2	The study teams and/or their contacts will reach out to people that are known to them through the SMARThealth Pregnancy study and through the wider network of the George Institute in India; additional relevant participants will also be identified through the scoping review.
Women finance self-help group lead	In-depth interview	1–2	
	Total *n*	50–80	

This study will exclude people who decline participation; people who do not speak and understand verbal communication in English or the local vernacular language (Telugu); and people below 18 years of age.

Informed written consent will be obtained from all participants by a member of the study team prior to the interviews.

### Outcome measures

The expected outcomes for the PRAMH study are:
•Outcome 1 (objective 1): A completed situational analysis tool, which will clarify perinatal mental health needs in the study setting, context, mental health policies and plans, mental health treatment coverage, district level health services, community setting, and monitoring and evaluation plans.•Outcome (objective 2): Learnings on perinatal mental health in rural Telangana, specifically in people's knowledge, beliefs, and attitudes, and in regard to context and implementation challenges and barriers of perinatal mental health assessment and intervention.•Outcome (objective 3): An implementation framework specifying the defined priorities, hypotheses, design and outcomes for a new future perinatal mental health intervention in rural Telangana.

## The SMARThealth Pregnancy And Mental Health (PRAMH) situational analysis

The PRAMH study will be composed of three components.
(1)Completion of situational analysis tool, using a desktop and literature review.(2)Analysis of context, barriers and facilitators in relation to perinatal mental health and related interventions, using in-depth interviews and focus group discussions(3)Development of a framework to guide a future intervention and implementation in the next phase of the study, using a set of theory of change workshops.Figure 1 outlines the study schema of formative and intervention development.

**Figure 1 F1:**
[figure not shown]
PRAMH study schema of formative and intervention development.

### Situational analysis tool

We will use a standardised situational analysis tool, adapted from the PRIME study/WHO-AIMS (53, 60). The situational analysis will begin with a comprehensive desktop and literature review to assess perinatal mental health, policies and initiatives at the country and state level. This will be complemented by a second phase involving in-depth interviews and focus groups to understand the current situation for women with perinatal mental health problems in selected rural settings.

The situational analysis will investigate seven themes, exploring context, (perinatal) mental health policies and plans, treatment coverage, district-level health services, community, monitoring and evaluation, key stakeholders.

Sources of data for the desktop review will include web pages, publicly available reports and other documents from state and national Ministries of Health and Welfare, the National Institute of Mental Health and Neurosciences (NIMHANS), National Family and Health Survey (NFHS) health surveillance reports, peer-reviewed research publications, and will be supplemented by personal communication with experts in the field.

### In-depth interviews

In-depth interviews (IDIs) will be conducted to understand local stakeholders’ perspectives on perinatal mental health and perinatal mental health conditions, existing approaches to cope with mental distress, as well as acceptability and feasibility of brief psychological interventions, and cultural and structural issues related to the implementation of the intervention. The design of the topic guides for the IDIs and FGDs will be informed by the themes of the situational analysis and concepts from Proctor et al.'s taxonomy of implementation science (61).

The IDIs will be conducted in Telangana with policymakers and planners, health professionals, and civil society members (see Table 1 above). IDIs will be also conducted for women and family members with lived experience who for reasons of health condition, stigma and discrimination, or other reasons, are unable to participate in focus group discussions. It is estimated that approximately 5–10 IDIs will be conducted in total (*n* = 10–20).

Members of the research team will be trained by the study lead in conducting qualitative interviews. The interviews will be conducted using a semi-structured interview guide. The in-depth interview topic guides will be informed by Kleinman's explanatory model interview (62, 63). Other studies have used qualitative interviews to assess barriers to women seeking and receiving help for perinatal mental health problems and developed questionnaires (64) and perspectives on antenatal mental health problems and to assess the potential for psychological interventions (65).

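### The planned total of 5–10 in-depth interviews disagrees with its own n of 10–20 and with the 11 interview categories (11–22 people) in Table 1

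*Protocol article*

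**What the plan says.** The article gives the number of in-depth interviews (IDIs) in three places.

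- **In-depth interviews section:** "approximately 5–10 IDIs will be conducted in total (*n* = 10–20"). The same section refers to Table 1 for the interviewees. It then adds a fallback: "IDIs will be also conducted for women and family members with lived experience", where illness, stigma or another reason keeps them out of a focus group. No number is given for these.
- **Table 1 (Recruitment and consent):** each interview category has its own row with n = 1–2, for example "Policymaker In-depth interview 1–2", "District health official/planner In-depth interview 1–2", "Obstetrician/gynaecologist In-depth interview 1–2" and "Women finance self-help group lead In-depth interview 1–2". Women and family members have focus group rows, for example "Women with lived experience Focus group discussion 10–15". The stated table total is 50–80.
- **Abstract (Methods/design):** the interviews are with policymakers, planners, "mental health professionals and other experts in perinatal mental health (*n* = 10–15").

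**The concern.** In a qualitative study with purposive sampling, the list of stakeholder categories and the number interviewed in each is the sampling plan. Here one quantity has several values that cannot all be true. Five to ten interviews cannot yield 10–20 interviewees unless people are interviewed in pairs, and they cannot give each of the 11 listed categories its own interview.

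A reader therefore cannot tell whether every category is meant to be interviewed, and cannot later judge whether the plan was met. If the low figure governed fieldwork, some categories would be dropped without the plan saying which. The fallback interviews with women and family members would also fall under the same overall figure and compete for the same places.

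**Working it through.** **Inputs**

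- In-depth interviews section: 5–10 interviews in total, n = 10–20.
- Table 1 interview rows, each 1–2:
  - 4 for policy and planning (policymaker, district official or planner, village head, mid-level provider)
  - 5 for health professionals (psychiatrist, psychologist, obstetrician/gynaecologist, PHC doctor, AYUSH doctor)
  - 2 for community (civil society organisation, self-help group lead)
- Table 1 focus group rows: 4, each 10–15.
- Table 1 total: 50–80.
- Abstract: 10–15 for interviews.

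**1. Can the plan's n = 10–20 be reproduced?** Yes.

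- Focus group rows: 4 × 10 = 40 and 4 × 15 = 60.
- Table total minus focus groups: 50 − 40 = 10 and 80 − 60 = 20, which is exactly 10–20.
- Direct count of interview rows: 4 + 5 + 2 = 11, so 11 × 1 = 11 and 11 × 2 = 22. This agrees with 10–20 to within one person at the lower end and two at the upper.

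**2. Can the 5–10 interviews be reproduced?** No.

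- Against Table 1 at one person per interview, the shortfall is 11 − 5 = 6 at the lower end and 22 − 10 = 12 at the upper.
- Against its own n, people per interview are 10 / 5 = 2 and 20 / 10 = 2. Pairing would reconcile the two figures, but the article describes no paired, joint or repeat interviews.
- The five health-professional rows alone give 5 × 1 = 5 to 5 × 2 = 10. That may be where the figure came from, but the sentence presents it as the overall total.

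**3. Coverage if 5–10 were followed.** With k interviews, one person each, and each person filling one category, at least 11 − k categories are left empty.

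| Interviews held | Categories in Table 1 | Minimum left empty |
|---|---|---|
| 5 | 11 | 6 |
| 10 | 11 | 1 |

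Each interview given to a woman or family member as a fallback raises the minimum by one.

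**4. The abstract.** Its 10–15 meets 5–10 only at 10. It lies inside 10–20, but its upper limit is 5 below 20 and 7 below 22.

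**5. The Table 1 total.** The rows sum to 11 + 40 = 51 and 22 + 60 = 82, against 50–80. This is the same rounding as in step 1 and not a separate error.

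**The case against.** The strongest reply is that this is one slip in a sentence hedged as an approximate estimate. The bracketed n fits Table 1, the section refers the reader to Table 1, and a team working from that table would leave no category empty. Most of this stands. It shows that 5–10 is the outlier and that the interviewee numbers are otherwise consistent. The hedge can excuse 10 against 11, but not 5 against 11 or 10 against 22.

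The abstract is also only partly a like-for-like comparison. Its wording does not clearly include village heads, the self-help group lead, or women and family members. It is weaker evidence of conflict than Table 1, though it remains a third range that the reader cannot place.

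A reader might infer that the health-system part of the analysis will have empty cells. The article does not support that. Categories go empty only if 5–10 is carried out in place of Table 1. The situational analysis tool is completed from a desktop and literature review, supplemented by communication with experts. Focus groups with community health workers and nurses and a theory of change workshop also contribute. Fewer interviews would thin the stakeholder evidence without necessarily leaving that part blank.

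A reader might also infer that the women and family members interviewed individually are missing from the sample size. They already have rows in Table 1 under focus groups, and the interview is offered to those who cannot attend one. They may therefore already be counted, but the article does not say.

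**Conclusion.** The point holds for the figure of 5–10 interviews. It is wrong as written by a factor of about two: 11 / 5 = 2.2 and 22 / 10 = 2.2 against Table 1, and exactly two against its own n. The abstract adds a range that matches neither.

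The possible loss of coverage, at least 1 to 6 of 11 categories, rests on three assumptions: that 5–10 is the operative number, that each interview has one participant, and that each participant represents one category. The second is the natural reading of Table 1, but the article does not state it.

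The study has no hypothesis test or power calculation, so no error rate or estimate is affected. This is a should-fix: a stated sample size that contradicts the sampling table and is cheap to correct.

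**What to change.** 1. In the In-depth interviews section, replace 5–10 with one interview count that matches Table 1: 11–22 with one participant per interview. If joint interviews are intended, say so and give the number of interviews and of interviewees separately.
2. Use the same range in the abstract, or state which subgroup its 10–15 covers.
3. State, in a footnote to Table 1, whether the fallback interviews with women and family members are counted within their existing rows or are additional. Adding a new row on top without settling this could count the same people twice.
4. Recompute the Table 1 total last. Its focus group rows sum to 40–60, while Table 2 gives 20–32 and the abstract 24–40, so a corrected total means little until those are reconciled.

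If 5–10 is a slip, the cost is wording and table totals, because the Table 1 interviews are already planned. If 5–10 is the real capacity for fieldwork between August and December 2022, the plan must instead say which Table 1 categories will not be interviewed, or find room for roughly twice as many interviews. The authors need to say which case applies.
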